## Abstract

**Background:**

Ruptures of the anterior cruciate ligament (ACL) are common injuries to the knee joint. Arthroscopic ACL replacement by autologous tendon grafts has established itself as a standard of care.

Data from both experimental and observational studies suggest that surgical reconstruction does not fully restore knee stability. Persisting anterior laxity may lead to recurrent episodes of giving-way and cartilage damage. This might at least in part depend on the method of graft fixation in the bony tunnels. Whereas resorbable screws are easy to handle, pins may better preserve graft tension. The objective of this study is to determine whether pinning of ACL grafts reduces residual anterior laxity six months after surgery as compared to screw fixation.

**Design/ Methods:**

SPOT is a randomised, controlled, patient and investigator blinded trial conducted at a single academic institution. Eligible patients are scheduled to arthroscopic ACL repair with triple-stranded hamstring grafts, conducted by a single, experienced surgeon. Intraoperatively, subjects willing to engage in this study will be randomised to transplant tethering with either resorbable screws or resorbable pins. No other changes apply to locally established treatment protocols. Patients and clinical investigators will remain blinded to the assigned fixation method until the six-month follow-up examination.

The primary outcome is the side-to-side (repaired to healthy knee) difference in anterior translation as measured by the KT-1000 arthrometer at a defined load (89 N) six months after surgery. A sample size of 54 patients will yield a power of 80% to detect a difference of 1.0 mm ± standard deviation 1.2 mm at a two-sided alpha of 5% with a t-test for independent samples.

Secondary outcomes (generic and disease-specific measures of quality of life, magnetic resonance imaging morphology of transplants and devices) will be handled in an exploratory fashion.

**Conclusion:**

SPOT aims at showing a reduction in anterior knee laxity after fixing ACL grafts by pins compared to screws.

## Background

Anterior cruciate ligament (ACL) rupture belongs to the most common musculoskeletal injuries in the western world. In the United States, 100,000 new cases occur each year, with 10% of all injuries leading to occupational disability [1]. In Germany, the prevalence of torn ACL among subjects between 20 and 35 years averages 0.4%. In the general population, the yearly incidence of ACL rupture reaches 32/100,000, but peaks to 70/100,000 in athletes [2].

An ACL deficient knee is at risk of developing secondary damage to the cartilage and is liable to undergo progressive intra-articular worsening. Roughly half of all acute ACL disruptions attend meniscus damage. Arthroscopic reconstruction surgery by autologous grafting emerged as the therapy of choice. Predictions call for 175,000 ACL replacements performed yearly in the United States. In Germany, around 50,000 patients undergo ACL repair each year.

Selecting the ideal graft remains an issue of debate. Randomized controlled trials suggest a lower degree of persistent laxity with bone-patellar-tendon-bone (BPTB) comparing with two-, three- or four-bundle hamstring (that is, semitendinosus and gracilis tendon) transplants (HT).

However, the biomechanical advantage does not frame higher patient satisfaction, or differences in scoring after long-term follow-up [3]. In contrast, harvesting BPTB grafts often produces notable donor site morbidity, and refractory kneeling pain [4,5].

Available data from randomized, quasi-randomized and uncontrolled trials signal a weighted mean difference of 2.28 mm (95% confidence interval [CI] 1.83 – 2.73 mm) in anterior laxity between the injured and healthy knee with HT reconstruction (see Figure 1) [3,6-16].

**Figure 1 F1:**
[figure not shown]
Persisting instability following ACL repair with HT autografts (KT-1000 measurements). Individual study results were weighted by their inverse variance to derive a common point estimate with 95% confidence interval (diamond).

Many features contribute to an unsatisfactory or failed ACL replacement, for example, imprecise tunnel positioning, the presence of degenerative changes, or the onset of arthrofibrosis.

The choice of tibial graft fixation affects later stability. The intact ACL has a tensile strength around 2200 N. To avoid loosening, the graft must be fixed under firm traction (around 40 N), with the knee in a smoothly flexed position. A common way to anchor the tibial end of the graft is by titanium or biodegradable interference screws, for example, the BioCryl^® ^(DePuy Mitek) screw that contains both resorbable poly-L-lactid and osteoconductive tricalcium phosphate (see Figure 2).

**Figure 2 F2:**
[figure not shown]
Appearance of the BioCryl^® ^screws (left, courtesy of DePuy Mitek), and their positioning (right).

However, in a recent biomechanical study, extracortical fixation devices like the EndoButton^® ^(Smith & Nephew) or RigidFix^® ^(DePuy Mitek) provided better strength than did the interference screws [17]. The possible advantage of RigidFix^® ^over other tethering methods is a splicing of strands, tightening the contact between the tendon surface and the bony tunnel over the entire graft circumference (see Figure 3).

**Figure 3 F3:**
[figure not shown]
Left: Positioning of RigidFix^® ^pins. Right: splicing of graft bundles leading to close adherence to the surrounding bone.

## Methods/ Design

### Objectives

The present study aims at comparing later laxity in subjects undergoing arthroscopic anterior cruciate ligament replacement with either RigidFix^® ^pinning or BioCryl^® ^screwing of HT grafts. Both implants are CE approved, and were introduced to ACL-repair in Germany in 2002.

We have secondary objectives in imagining graft incorporation by MRI-scanning, functional results, residual pain, resumption of occupational and leisure activity, and quality of life by generic and disease-specific questionnaires.

### Primary endpoint

We pose the primary hypothesis that the RigidFix^® ^system preserves graft tension gained during surgery, and leads to lower KT-1000 arthrometer side-to-side differences than the BioCryl^® ^screw after six months of follow-up.

Specifically, we will test the hypothesis that RigidFix^® ^decreases the average difference gained with interference screws by 1.0 ± standard deviation 1.2 mm. The investigators consider this difference clinically sound, important, and measurable by KT-1000 arthrometer testing. Twenty-four subjects a treatment arm will allow for detecting this difference with an 80% chance at a two-sided alpha-level of 5%. Assuming a drop-out rate of 10%, 54 patients will be enrolled in this study.

### Secondary endpoints

As secondary endpoints, we consider functional outcomes by means of the Lysholm scale, the Tegner score, and the International Knee Documentation Committee evaluation form (IKDC) in its German translation, 2000 revision [18]. Besides disease-specific items, this questionnaire also contains the Short-Form 36 (SF-36) generic health assessment tool. The noted instruments have proven reliability, validity, and responsiveness for use in clinical research.

Confirmatory testing will apply for the primary endpoint only. All secondary endpoints will be addressed in an exploratory fashion.

### Design

SPOT is a patient and investigator blinded, randomised controlled trial conducted at a single academic institution.

Randomisation is carried out in the operating theatre shortly before transplant fixation, with random codes drawn from sealed envelopes. We use block-randomisation with five subjects a block following a computer-generated random list [19].

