### Surgery and rehabilitation

All devices and instrumentations used in this clinical investigation bear the CE mark. They belong to the regular implants used for ACL repair at the study hospital since 2002. Except different graft anchoring, similar treatments apply to patients in both study groups. All participants undergo internationally accepted surgically procedures by a single surgeon ([name]) with extensive experience in ACL repair using both the BioCryl^® ^screw and RigidFix^® ^cross pins. Also, postoperative care and rehabilitation programs do not differ from those employed outside a clinical trial.

All repairs are carried out under general anaesthesia, with the patient in a supine position. Perioperative antibiotic prophylaxis comprises 2 g of cefotiam. Patients receive 40 mg of enoxaparin daily for prophylaxis of thromboembolic events until full weight bearing.

The knee joint is accessed through two to three standard portals. Meniscal injuries are addressed with partial resection or repair.

Hamstring tendons are harvested via a small incision over the insertion of the pes anserinus at the anterior medial tibia by a closed tendon stripper, and prepared as triple-stranded grafts.

Tibial and femoral tunnels are drilled to approximate graft thickness (usually 8 to 9 mm) with the use of a guiding wire. Grafts are fixed with the knee in 30° flexion to achieve firm tension.

Postoperatively, the knee is stabilized for three days by a zero-degree splint. Afterwards, flexion is limited to 90° by a Secutec^® ^orthosis for six weeks. Patients are allowed partial weight bearing with walking crutches. Subjects are prescribed intense physical therapy for motion exercise, and to strengthen thigh muscles. Normally, full range of motion and weight bearing is achieved until week 12 after surgery.

Patients in the experimental group have their grafts secured by tibial and femoral RigidFix^® ^pinning. Patient in the control group receive tibial and femoral BioCryl^® ^screws.

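### A fixed block of five cannot give the 1:1 allocation behind 24 per arm, and its constant size is a moderate concealment weakness with one surgeon; the power cost is small

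*Protocol article*

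**What the plan says.** All places are in the protocol article.

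- **Arms.** The Abstract (Design/Methods) has patients "randomised to transplant tethering with either resorbable screws or resorbable pins".
- **Block size.** Design states: "We use block-randomisation with five subjects a block following a computer-generated random list". It gives one size, no allocation ratio and no rule for dividing five patients between two arms.
- **Timing and concealment.** The same section places randomisation in theatre, just before the graft is fixed, "with random codes drawn from sealed envelopes".
- **Sample size.** Primary endpoint states: "Twenty-four subjects a treatment arm will allow for detecting this difference with an 80% chance", for a pin system that "decreases the average difference gained with interference screws by 1.0 ± standard deviation 1.2 mm". It goes on: "Assuming a drop-out rate of 10%, 54 patients will be enrolled in this study". Equal arms are implied.
- **Operator.** Surgery and rehabilitation states: "All participants undergo internationally accepted surgically procedures by a single surgeon". Under Intraoperative assessments the same surgeon rates how the implants handled, so he knows which device each patient received.

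**The concern.** There are two separate issues, with different causes.

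**Balance.** Blocking is there to keep the arms close to their planned ratio. Five is odd, so no complete block can be balanced, and the block size does not fit the equal arms assumed in the sample size. The final split depends on a rule that the text does not give.

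**Concealment.** With one centre, one operator and one constant block size, the surgeon sees the whole sequence in order. If he knows the size, he can sometimes work out the next allocation before the envelope is opened. What is then open to influence is whether or when the envelope is drawn, and the surgical steps before fixation.

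**Working it through.** **1. The plan's own figure.** Inputs from Primary endpoint: difference 1.0 mm, SD 1.2 mm, two-sided alpha 5%. For arms n1 and n2, power comes from the noncentral t with n1 + n2 − 2 degrees of freedom and noncentrality 1.0 / (1.2 × √(1/n1 + 1/n2)).

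- 24:24 gives noncentrality 2.887 and power 80.7%; 23:23 gives 78.9%. So 24 per arm is right.
- 48 / 0.9 = 53.3, rounded up to 54. Also right.

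**2. Final split at 54.** This is ten full blocks plus four places of an eleventh. The rule is not stated, so two readings are shown.

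*(a) Each block 3:2 or 2:3 with equal chance.* One arm receives 20 + Binomial(10, ½) from the full blocks, plus 1, 2 or 3 from the last four places with probabilities 0.2, 0.6 and 0.2.

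- P(27:27) = (210 × 0.2 + 252 × 0.6 + 210 × 0.2) / 1024 = 235.2 / 1024 = 23.0%.
- P(difference of 6 or more) = 2 × (0.0518 + 0.0148 + 0.0025 + 0.0002) = 13.9%.
- For comparison, simple randomisation of 54 gives a difference of 6 or more in 49.7% of lists.

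*(b) Always 3:2 for the same arm.* The full blocks give 30:20. The last four places add 2 to the favoured arm (probability 0.6) or 3 (0.4). The split is 32:22 or 33:21.

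**3. Power after 10% dropout in each arm.**

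| Enrolled | Evaluable | Power |
|---|---|---|
| 27:27 | 24.3:24.3 | 81.2% |
| (a), averaged over lists | – | 81.0% |
| 32:22 | 28.8:19.8 | 79.8% |
| 33:21 | 29.7:18.9 | 79.2% |

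**4. Predictability.** Assume a guesser who knows the block size (or the possible sizes) and all past allocations. The fixed schemes were enumerated in full. Figures are the chance of a correct best guess by position in the block.

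- Five, random direction: 0.5, 0.6, 0.6, 0.7, 0.7; mean 3.1/5 = 62%. Certain: (0.1 + 0.4)/5 = 10%.
- Five, always 3:2: 0.6, 0.6, 0.7, 0.7, 1.0; mean 3.6/5 = 72%. Certain: (0.1 + 0.4 + 1.0)/5 = 30%.
- Fixed 4: 71% best guess, 33% certain.
- Fixed 6: 68% best guess, 25% certain.
- Sizes 4 and 6 mixed at random (simulated; the guesser knows only that these two sizes are used): 69% best guess, about 6% certain.

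**5. Balance with mixed 4 and 6.** Every completed block is balanced and has even length, so the 54th place falls at the end of a block or after its second or fourth place. The difference is then 0 or 2.

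**The case against.** Several stronger readings are tempting, and the documents do not support them.

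- **That the trial loses its power.** A reader might infer this from 32:22. The text never says that blocks are always 3:2, and the equal arms in the sample size speak against it. With random direction the average power is 81.0%. Even a 27:21 split of 48 evaluable patients gives 80.1%. Rounding the always-3:2 case to 29:19 gives 78.9%, but 90% of 32:22 is 28.8:19.8, which gives 79.8%.
- **That the odd size makes allocations predictable.** It does not. With random direction, fives are less predictable than fixed blocks of 4 or 6. The odd size causes the imbalance; the constant size, if known, causes the predictability.
- **That foreknowledge biases how the graft is tensioned and fixed.** The envelope is drawn just before fixation, so the surgeon knows the arm at that step under any scheme. Only earlier steps, or withholding or delaying the draw, could be affected. Screening before admission and written consent narrow that discretion without removing it. Independent examiners who did not operate, working with both knees dressed, protect the measurement but not who enters or how surgery proceeds before the draw.
- **That the list was in the wrong hands.** The article does not say who made or held it, who draws the envelope, or whether the surgeon was told the block size. A condensed article may leave this to the full protocol, so it is not a fault here. His knowing the size is an assumption.

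It is also fair to say that the remedy does not lower best-guess accuracy in every case. Always guessing the arm that is behind, with no knowledge of block sizes, is right about 69% of the time with mixed 4 and 6, against 57% with random-direction fives.

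What stands is the misfit between block size and equal arms, and a moderate weakness from a constant size with a sole operator.

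**Conclusion.** The point holds in a limited form and should be fixed; it is not a fatal flaw. The stated block size cannot deliver the allocation on which the sample size rests. The numerical harm is modest: exact balance in about 23% of lists and a gap of 6 or more in about 14% with random direction, or 32:22 to 33:21 if always 3:2. At worst power falls about 2 points below the 81.2% that equal arms would give, and less than 1 point below the stated 80%. The sample size calculation itself is correct.

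The concealment weakness is moderate and conditional. It needs the surgeon to know the block size and to keep track of the sequence; 10% to 30% of allocations are then certain. The power figures assume the planned difference and SD and an equal 10% dropout in both arms. The ranges reflect only the unstated split rule.

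**What to change.** In Design, replace the block of five by 1:1 permuted blocks of randomly varying even size (for example 4 and 6), say that the sizes vary, and do not disclose them to the surgeon. If recruitment has begun, apply the new list from the next unused envelope and keep the allocations already made.

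For a full list of 54 this holds the final imbalance to 2 and reduces certain allocations from 10% to 30% down to about 6%. If it starts part-way, the limit applies to the patients still to be randomised, and any imbalance already present carries over.

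The cost is a new random list, new envelopes and one changed sentence. The small downside is a best-guess accuracy of about 69%. That is below the 72% of always-3:2 blocks but above the 62% of random-direction fives, so the gain is in balance and in fewer certain allocations, not in making every guess harder.

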### Inclusion criteria

Men and women (providing that they are not pregnant) being at least 18 years old are recruited to this trial. Subjects may engage in this study if they

- faced a **first one-sided total or subtotal rupture of the anterior cruciate ligament**, proven either by arthroscopy or MRI-scanning

- had met an acute knee distorsion event likely to have caused the index injury at least six weeks before scheduled repair

- have been physically examined in the ambulatory of the study hospital before assigning an admission date, and were screened and considered suitable to enter this trial by one of the investigators

Also, patients must be able to give voluntary written informed consent, and to comply with the post operative follow up regime

### Exclusion criteria

We exclude patients

- with related lower limb fractures

- with active infection affecting the limb subject to needed treatment

- who have previously took part in this investigation or who are taking part in another clinical investigation

- with contraindications for MRI-scanning (that is, large indwelling orthopaedic implants made of metals others than titanium, or pacemakers)

### Ethical considerations

This protocol and all accompanying documents were approved by the local Institutional Review Board (IRB).

According to IRB recommendations and requirements, information leaflets explicitly note that "a benefit from participation in this trial cannot be guaranteed."

We will stress the principle of randomisation as "treatment assignment by chance, without the possibility of the investigator, other health care professionals involved in this study, or the patient influencing the choice of treatment." We also tell patients that, as long as they keep agreement in participation, they will not know their assigned treatment until the six-month follow-up visit.

We will notify the IRB of any significant changes to the protocol. Also, we will notify the IRB within ten working days of the discovery of any severe adverse events which occur during this investigation.

Confidentiality of subject data will always be maintained. Subject anonymity will be guaranteed and all documentation about a subject (including radiographs) will be kept in secure location.

This investigation strictly adheres to the relevant articles of the Declaration of Helsinki as adopted by the 18^th ^World Medical Assembly in 1964 and its later revisions, as well as to principles of GCP, developed within the Expert Working Group (Efficacy) of the International Conference on Harmonisation of Technical Requirements for Registration of Pharmaceuticals for Human Use (ICH).

### Surgery and rehabilitation

All devices and instrumentations used in this clinical investigation bear the CE mark. They belong to the regular implants used for ACL repair at the study hospital since 2002. Except different graft anchoring, similar treatments apply to patients in both study groups. All participants undergo internationally accepted surgically procedures by a single surgeon ([name]) with extensive experience in ACL repair using both the BioCryl^® ^screw and RigidFix^® ^cross pins. Also, postoperative care and rehabilitation programs do not differ from those employed outside a clinical trial.

All repairs are carried out under general anaesthesia, with the patient in a supine position. Perioperative antibiotic prophylaxis comprises 2 g of cefotiam. Patients receive 40 mg of enoxaparin daily for prophylaxis of thromboembolic events until full weight bearing.

The knee joint is accessed through two to three standard portals. Meniscal injuries are addressed with partial resection or repair.

Hamstring tendons are harvested via a small incision over the insertion of the pes anserinus at the anterior medial tibia by a closed tendon stripper, and prepared as triple-stranded grafts.

Tibial and femoral tunnels are drilled to approximate graft thickness (usually 8 to 9 mm) with the use of a guiding wire. Grafts are fixed with the knee in 30° flexion to achieve firm tension.

Postoperatively, the knee is stabilized for three days by a zero-degree splint. Afterwards, flexion is limited to 90° by a Secutec^® ^orthosis for six weeks. Patients are allowed partial weight bearing with walking crutches. Subjects are prescribed intense physical therapy for motion exercise, and to strengthen thigh muscles. Normally, full range of motion and weight bearing is achieved until week 12 after surgery.

Patients in the experimental group have their grafts secured by tibial and femoral RigidFix^® ^pinning. Patient in the control group receive tibial and femoral BioCryl^® ^screws.

### Baseline assessment

Each subject considered eligible for entry into this investigation has the following information and procedures recorded at the pre-investigational examination:

- Demographic details including date of birth and gender

- Medical history, coexisting diseases, and accompanying medication

- Physical examination, including circumferential measurement of both legs at defined landmarks, Lachman and pivot shift tests, KT-1000 arthrometer objectifying of instability, one-legged hop test, Lysholm, Tegner, and IKDC scores, knee and kneeling pain measured by visual analogue scales

- Radiographic examination, including a conventional roentgenogram of the injured knee in anteroposterior and lateral projection, and a preoperative MRI scan according to local standards

### Intraoperative assessments

During surgery, we record procedure details in the electronic CRF. We assess the duration of surgery (from cut to skin closure), and operating theatre time (from induction of anaesthesia to arrival at the recovery room). A clinical knee examination is performed and documented with the subjects under general anaesthesia and relaxation. Arthroscopy findings (accompanying injuries to or degenerative changes of the cruciate or collateral ligaments, menisci, or cartilage) are recorded by video and/ or hard copy images.

We document eventual blood loss, and any other adverse event occurring during surgery.

The responsible surgeon judges the handling of implants and his overall satisfaction with the intraoperative result using five-point Likert scales. We detail any problems or complications on an Adverse Events form.

